#### Tell My Story

Researchers will interview women and discuss family practices including lifestyle, stressors, social support, cultural practices and childrearing. There will be the option for women to do a one-off in-depth interview or to take part in repeated interviews antenatally and until the infant is six months old. Interviews will explore Indigenous perspectives of culturally safe care (acceptability) and what constitutes social, cultural and clinical risk and wellbeing for Aboriginal and Torres Strait Islander women. Women will be asked about their relationships with healthcare providers, their experiences with maternity services and how these impact engagement, health choices and outcomes.

Interviews will be recorded using a digital recorder and observations recorded using hand written notes. Antenatal and postnatal interviews will be conducted in a convenient location for women – in the home, clinic or hospital. Participants will be provided with a AU$30 gift voucher as a thank-you for their time.

#### Staff surveys, interviews and focus groups

##### Staff interviews and focus groups

All staff who have provided specialised maternity care for women having Aboriginal and/or Torres Strait Islander babies at either the MMH (including Birthing in Our Community) or at the RBWH (including the Ngarrama Indigenous Service) will be invited to participate in staff interviews and focus groups. This includes but is not limited to exit interviews with staff leaving or who have left the service. These interviews will explore the experiences of staff working within the programs and identify any recommendations for future and existing services. This will assist with identifying the ‘key ingredients’ of a best practice model of maternity care as well as evaluating the acceptability, feasibility, and cost-effectiveness of the different models of care. Semi-structured interviews will be conducted over the phone, in person or in small groups. With the staff members’ permission, these interviews will be audio-recorded.

##### Staff surveys

In order to evaluate the sustainability of the models from a workforce perspective, annual quantitative surveys will be conducted with staff involved in the program. A comparison group of MMH and RBWH caseload midwives will also be invited to participate in selected surveys to assess whether there is a significant difference in workload, daily activities and work-related stress between the caseload midwifery teams. Online and anonymous surveys will be conducted with staff. These will be voluntary and confidential, and likely include the Maslach Burnout Inventory or Copenhagen Burnout Inventory [38], the Attitudes to Professional Role, Caseload Midwifery Industrial Agreement Questionnaire, Time in Motion Study, Kessler Psychological Distress and Wellbeing Scale as well as questions about team cohesion, meeting goals, cultural capability of staff, and suggestions for improvements.

### Outcome measures

#### Primary outcome measures (all groups)

Proportion of women giving birth preterm (< 37 weeks gestation)Proportion of women who attend five or more antenatal visits during pregnancyProportion of women smoking after 20 weeks gestationProportion of women exclusively breast-feeding at discharge from hospital.

#### Secondary outcome measures (all groups where reliable data is available)

Gestation at first antenatal visit to a health provider, at booking into hospital (weeks, Mean, Median, Range, First trimester (Yes/No)), Number of total antenatal visits (Mean, SD, Median, Range, < 5 visits, 5 and more visits)The proportion of women with modifiable risk factors for preterm birth (i.e. inadequate antenatal care, smoking, stress and missing data in these fields)Smoking status at booking (Yes/No), during the first 20 weeks (Yes/No), and after the first 20 weeks (Yes/No), at discharge and six months postnatal, Number of cigarettes intake each day if smoking (Mean, SD)The proportion of women who attended antenatal education sessions (Yes/No)Pharmacological analgesia in labour (Epidural/spinal analgesia, Narcotic analgesia, Nitrous oxide gas)Onset of labour (Induced, No labour, Spontaneous)Mode of birth (Non-instrumental vaginal birth, Instrumental vaginal birth, Elective Caesarean section, Emergency Caesarean section)Management of third stage labour (Active, Physiological)Postpartum haemorrhage (< 500; 500–999; 1000-1499; 1500 ml and more or with blood transfusion)Perineal trauma status (Intact/1st degree tear, 2nd degree tear, 3rd/4th degree tear).Episiotomy (Yes/No)Women who had a known caregiver for labour and birth (Yes/No)Birth weight (grams, Mean, SD, < 2500 g, 2500 g or more)Apgar score 5 min (< 7, 7 or above)Admission to a separate neonatal nursery (Yes/No)Perinatal outcomes (Liveborn survived, Liveborn neonatal death prior to discharge from hospital, Stillbirth)Cause of perinatal deathsAntenatal intention to breastfeed (Yes/No)Women exclusively breastfeeding at discharge from hospital following birth (Yes/No), at two months postnatal (Yes/No), and six months postnatal (Yes/No)Mother readmission to hospital up to six months postpartum (Yes/No)Infant readmission to hospital up to six months of age (Yes/No)Length of stay in hospital for mothers and infants following birth (Mean, Median, Range)Cost of care per mother/infant pair during pregnancy, birth, postnatal until mother six weeks postpartum and baby 28 days after birthNegative life events scale – full extended version – at booking-in and six months postnatal (Yes/No, Number of events)Modified Kessler Psychological Distress Scale (K5) score at booking-in, 36 weeks gestation, two and six months postnatalEdinburgh Postnatal Depression Scale score at booking-in and six months postnatalAges and Stages Questionnaire score at two and six months postnatalBayley III Cognitive, Language and Motor Skills score at six months postnatal

Note, all tools will be scored according to their recommended guidelines and outcomes reported accordingly.

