## Background

Maternal and infant health disparities have persisted between Aboriginal and Torres Strait Islander people and non-Indigenous Australians, with Aboriginal and Torres Strait Islander women having disproportionately higher rates of: maternal mortality (~ 3 times higher) [1]; preterm births (14% vs. 8%); low birth weight infants (liveborn: 12% vs. 6%); and perinatal deaths (12 vs. 9/1000) [2, 3]. Preterm birth is a leading cause of perinatal mortality, serious neonatal morbidity, and moderate to severe childhood disability [4]. It contributes to more than two-thirds of perinatal mortality (fetal loss and neonatal death) [5] and is associated with diabetes, cardiovascular and renal disease in adulthood [6]. Queensland [7] and Western Australian [8] research suggests the majority of perinatal deaths are associated with preterm birth and low birth weight, which in turn are linked to modifiable risk factors: maternal psychosocial stress [9], infections in pregnancy [10], smoking in pregnancy [11], limited maternal education and young maternal age [12]. An Australian Indigenous study found preterm births and perinatal deaths decrease as the number of antenatal consultations increases [13]. Targeting the antenatal period with interventions that are culturally safe and high quality are essential to addressing these health disparities [14–16].

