### Study design

This study underwent peer review by the funding body, the National Health and Medical Research Council*.* This study will consist of a prospective cohort study comparing:*Maternal and infant health outcomes*: women booked to receive maternity care through MMH or RBWH, by model of care and Aboriginal and Torres Strait Islander status of baby and/or mother (see Table 3). Routinely collected clinical outcomes for mothers and infants will provide data on the effectiveness of the programs since they commenced in late 2013 and be compared across groups for the duration of the study (ending in 2019), and to baseline data for both hospitals (2009–2013). Infant assessments will be undertaken at two and 6 months postnatally for Groups 1 and 4.*Service acceptability, effectiveness and cost-effectiveness:* Maternal surveys will be undertaken as early as possible antenatally (~ 20 weeks and 36 weeks antenatally, two and six months postnatally). An ethnographic component will also explore the pregnancy and early parenting (to six months postnatal) experiences of ~ 20 women from each Birthing in Our Community and the Ngarrama Service using a longitudinal, ethnographic approach: ‘Tell My Story’ substudy. Cost-effectiveness analysis will be conducted from the broader ‘societal’ perspective which will include not only the cost to the hospital (Routine data) but the cost to the women (Women’s surveys) and partner organisations (Routine data).*Service sustainability and feasibility:* Staff perspectives and experiences will be compared across the services to determine the sustainability and feasibility from a workforce perspective.

**Table 3 Tab3:** Timeline of groups by model of care and research data available

Year	2009	2010	2011	2012	2013	2014	2015	2016	2017	2018	2019
Groups by model of care						Group 1: Birthing in Our Community, MMH (Indigenous)					
	Group 2: Standard care, MMH (Indigenous)										
	Group 3: Standard care, MMH (Non-Indigenous)										
						Group 4: Ngarrama Indigenous Maternity Service, RBWH (Indigenous)					
	Group 5: Standard care, RBWH (Indigenous)										
	Group 6: Standard care, RBWH (Non-Indigenous)										
Research data (Groups)	*Baseline*					*Study period*					
	Routine Data (2, 3, 5, 6)					Routine Data (1–6)					
						Women’s Surveys (1, 2, 4, 5)					
						Tell My Story (1, 4)					
						Infant Assessments (1, 2, 4, 5)					
						Staff Interviews (1, 4)					

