### Data collection

#### Routinely collected clinical and costing data

Data for each mother/infant dyad at the MMH will be collected from several sources. MMH obstetric (MatriX), neonatal database and expenditure data (Australian activity based funding Diagnosis Related Groups [DRG] codes) will provide detailed patient-level information on inpatient contacts for the mother and baby. Routinely collected data including expenditure data will be collected from the RBWH where it will be coded before being merged with the study database. Perinatal data will also be extracted from the Queensland Health database.

The IUIH (MMeX) and ATSICHS (Medical Director and Pracsoft; MMeX) routinely collect data on service delivery (access, clinical data, e.g. immunisations, and expenditure data) which will also be collected. The clinical and costing outcomes data will be derived from routinely collected information and survey data.

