Culturally safe aspects of care (importance, satisfaction)	✓		✓	
Felt respected & understood by hospital staff (by area)			✓	
Felt treated poorly or judged by staff			✓	
Satisfaction with care, recommend to others		✓		
Known midwife present during labour/birth			✓	
Attendance of group antenatal classes		✓		
Smoking				
Current smoking status, including number of cigarettes per day	D	✓	✓	✓
Attempts to quit	D	✓		
Advised to quit by health staff		✓		
Smoking support received, perceptions		✓		
Smoking household members	✓	✓		✓
Feeding baby				
Previous breastfeeding experiences, inc. difficulties	D	✓		
Intentions to breastfeed, inc. duration	D	✓		
Confidence to breastfeed		✓		
Experience of breastfeeding, inc. initiation			✓	
Use of formula, inc. reasons, age of baby			✓	
What baby has been fed in past 24h			✓	✓
Where received feeding information			✓	
Use of commercial baby food				✓
Reasons for starting solids				✓
Partner involvement				
Partner’s feelings about pregnancy	✓			
Baby’s father & father figures (involvement, attended visits, support services)				✓
Social and emotional wellbeing				
Negative life events - full extended version	✓	✓		✓
Additional worries experienced	✓	✓		✓
Family separations			✓	
Positive wellbeing scale	✓	✓	✓	✓
Modified Kessler Psychological Distress Scale (K5)	✓	✓	✓	✓
Edinburgh Postnatal Depression Scale	D			✓
Practical Social Support Scale	✓			
Social support available, inc. partner		✓		
Out-of-pocket costs				
Time spent, support person, carer, transport, food & drink		✓		
All services accessed for pregnancy/birth/baby, number of visits, out of pocket cost per visit (i.e. not refunded by Medicare)			✓	
Out of pocket cost of medicines during pregnancy/birth/baby			✓	
Infant development				
Ages and Stages Questionnaire			✓	✓
Bayley III Cognitive, Language and Motor Skills (face-to-face assessment)				✓

Note: D = clinical data available

Participants will be provided with an AU$10 gift card after completing the booking-in and 36 weeks antenatal surveys and a large tote bag at 36 weeks. An AU$30 gift card and a small toy or bib/blanket will be given for the two and six-month postnatal surveys to thank women for their time. Women who participate with their infant in the Bayley assessment will receive an additional AU$10 gift card upon completion.

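### As worded, a secondary outcome counts missing data as a modifiable risk factor for preterm birth, so unequal completeness between models of care would read as unequal risk

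*Protocol article*

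**What the plan says.** The list of secondary outcomes includes the share of women who have a modifiable risk factor for preterm birth, and a bracket defines such factors: "i.e. inadequate antenatal care, smoking, stress and missing data in these fields". The heading over the list applies it to all groups, with a qualifier: "Secondary outcome measures (all groups where reliable data is available".

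The Background gives the article's own account of modifiable risk factors. It names stress, infection, smoking, low education and young age. Missing data is not among them.

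On data sources, Table 3 shows "Routine Data (1–6" for the study period but "Women’s Surveys (1, 2, 4, 5" for the surveys, so Groups 3 and 6 are not surveyed. The 2009–2013 baseline has routine data only. Table 5 places the "Modified Kessler Psychological Distress Scale (K5" and the negative life events scale among the survey items, and neither carries the D that marks clinical data as available. Survey participation needs individual consent, whereas a consent waiver is being sought for routine data.

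The quantitative analysis section presents outcome measures as relative risks with 95% confidence intervals, tests at the 0.05 level, and makes no exception for this item.

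**The concern.** The abbreviation that opens the bracket introduces a definition, and missing data is its fourth member, beside inadequate antenatal care, smoking and stress. An analyst who follows the text puts a woman with a blank field into the numerator. The resulting proportion mixes risk with data capture, and the planned comparison between models then picks up differences in either. A model with more complete data would look safer with no change in any woman's risk. A real reduction could also be hidden if the better model had the less complete data.

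This is not a gap that an unseen analysis plan would be expected to fill. The article itself fixes the definition, and fixes it badly.

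**Working it through.** **Is there a figure to reproduce?** The article states none for this outcome. Two inputs are borrowed from Table 4 for illustration: 350 women per arm and a 42% prevalence (the starting rate for smoking after 20 weeks). As a check on them, the usual two-proportion power formula (pooled variance under the null, two-sided 0.05, n = 350 per arm) returns 0.924, 0.858, 0.801 and 0.942 for the four rows of Table 4, matching the stated powers.

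**Formula.** Let p be the true prevalence and m the share of women with the field missing, with missingness independent of risk. Counting a blank as a risk factor gives

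observed proportion = m + (1 − m)p = p + m(1 − p).

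This holds for a single factor. It also holds for an any-of composite, if p is the share with at least one factor and m the share with at least one blank field.

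**No true difference, p = 42% in both arms.** The missing rates are assumptions. The relative risk is the arm with more missing data over the arm with less.

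| Missing | Observed | Relative risk | Chance of p < 0.05 at 350 per arm |
|---|---|---|---|
| 5% vs 10% | 0.42 + 0.05 × 0.58 = 44.9%; 0.42 + 0.10 × 0.58 = 47.8% | 0.478/0.449 = 1.06 | 12% |
| 5% vs 20% | 44.9%; 0.42 + 0.20 × 0.58 = 53.6% | 0.536/0.449 = 1.19 | 63% |
| 10% vs 30% | 47.8%; 0.42 + 0.30 × 0.58 = 59.4% | 0.594/0.478 = 1.24 | 87% |

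The nominal chance is 5%.

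**Sensitivity to p, at 5% vs 20% missing.** With p = 31%, the relative risk is 0.448/0.3445 = 1.30. With p = 60%, it is 0.68/0.62 = 1.10.

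**Masking.** Take a true 42% vs 31% (power 0.858 at 350 per arm), with no missing data in the 42% arm. If the 31% arm has 10% missing, its observed rate is 0.31 + 0.10 × 0.69 = 37.9%, and power falls to 0.197. The observed rates become equal when m = (0.42 − 0.31)/0.69, about 16%.

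**With missing data out of the definition.** Under the same independence assumption, equal true prevalence gives a relative risk of 1.00 whatever the missing rates.

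**Where could completeness differ?** Table 5 marks current smoking as available from clinical data at the first survey. Attendance at five or more antenatal visits is a primary outcome for all groups. Stress is the exposed component: the two nearest scales come only from consenting survey respondents in Groups 1, 2, 4 and 5, and response may differ between those groups.

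**The case against.** The strongest reply is that the bracket was meant as a reporting list. Brackets elsewhere in the same list often set out levels to be tabulated, missing data is plainly not a risk factor, and the Background does not call it one. On that reading the item asks for three factors plus a data-quality line, and there is no bias. That reading is possible and may be the intent. But the text introduces a definition of risk factors and puts missing data inside it. Nothing tells the analyst to keep it out of the numerator.

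A second reply is that the heading's reliable-data qualifier handles groups without surveys. It may allow Groups 3 and 6 to be left out. It does not take missing data out of the definition, and it does not equalise survey response among Groups 1, 2, 4 and 5.

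A third reply is that the consequence is limited. This stands: antenatal attendance and late smoking are primary outcomes in their own right, the distress and life-events scores are separate secondary outcomes, and no power figure depends on this item.

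A reader might also infer four stronger points that the article does not support:

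- **That the proportion must be 100% in Groups 3 and 6.** This requires stress to come from the survey scales and those groups to be kept in. The item names no instrument, the Edinburgh depression scale has a clinical-data mark at the first survey, and the heading permits omission.
- **That RBWH supplies a single extract against several MMH sources.** The article does say "Data for each mother/infant dyad at the MMH will be collected from several sources", but it describes no single RBWH extract, and it adds perinatal data from the Queensland Health database without limiting them to MMH.
- **That a known midwife means fuller records.** The article does not say this.
- **That the planned mediation analysis inherits the problem.** No mediators are named.

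**Conclusion.** The definition is wrong as written: a blank field counts toward a proportion that is to be compared between models of care. The arithmetic consequence is certain if the text is followed and completeness differs. Whether and how far completeness differs is not documented, and it is plausible mainly for stress. Over the assumed missing rates, with no true difference and p = 42%, the spurious relative risk runs from 1.06 to 1.24. These figures are illustrations that rest on the assumed rates, on missingness independent of risk, and on the borrowed 350 per arm, which may not match the number surveyed. The real size and direction are unknown. The point concerns one secondary outcome and does not touch the primary outcomes. It deserves correction before analysis because the correction is simple.

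**What to change.** Delete the last six words of "i.e. inadequate antenatal care, smoking, stress and missing data in these fields" from the definition. Compute each factor among women with that field recorded. Report percent missing by field and group as a separate line, which also serves the authors if a data-quality line was what they intended. State which instrument or record defines stress. If it is one of the survey scales, limit that component to surveyed women in Groups 1, 2, 4 and 5.

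The cost is one phrase and a short extra table; no new data are needed. The downside is smaller denominators, chiefly for stress. Observed-case proportions can still be biased if missingness is related to risk, so the missing-data line should be read beside them.

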### Data analysis and management

#### Quantitative

Clinical data will initially be collected in a re­identifiable form (via the unique patient identifier) so that it can be linked with data obtained from other sources (e.g. surveys), to enable the economic analyses to be undertaken. Once merged, identifiers will be removed and only the coded number will remain.

Quantitative analyses will compare the difference in clinical outcomes between Birthing in Our Community (intervention), the Ngarrama Service (concurrent control), standard care (historical and concurrent control), and also non-Indigenous women and babies (historical and concurrent control) at MMH and RBWH.

Data on all women attending either hospital during the study period will be extracted. Women transferring in from other hospital or rural and remote areas for higher-level services (variable available), and those with no antenatal care will be excluded from analysis. Analyses will be by birth model of care and women with multiple births and their infants with identified fetal anomaly will be excluded from analysis unless noted otherwise.

Initial bivariate analysis will investigate possible differences between the cohorts for baseline socio-demographic (socio-economic status), and clinical characteristics (e.g. age, parity, body mass index, smoking, obstetric history) that could affect outcome measures. Dependent on data type, analysis will be undertaken using an independent samples t-test, Mann-Whitney U test or chi-squared test. Outcome measures will be presented using relative risks with 95% confidence intervals. Multivariate logistic, linear regression models and propensity score matching will be used to adjust for confounders. Longitudinal outcomes (e.g. breastfeeding) will be analysed with generalized estimating equations to account for the correlation between observations repeated in the same person. To understand the mechanism or process that underlies the effect of model of care on outcomes, mediation analysis will be conducted to identify if and to what extent the other variables explains the relationship. All withdrawals, losses to follow-up, and deaths will be reported. Analysis will be performed with SPSS Version 22.0/Stata 14.0 and statistical significance will be at the 0.05 level.

Survey data will be uploaded from iPads/tablet computers, Qualtrics or other software tools such as Remark (for the printed versions) to a dedicated spreadsheet and subjected to simple descriptive analysis using SPSS/Stata. Bayley-III data at the six-month infant assessment will be scored by the research assistant in real time (i.e. as the assessment proceeds) using the age-standardized Bayley Record and Score Forms, and associated Tables to give norm-referenced scores. These scores will then be uploaded onto the project specific database. Staff surveys will be analysed using SPSS/Stata to test for significant trends and potential differences between groups.

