In developing the evaluation of the Birthing in Our Community program we aimed to compare outcomes for mothers and infants with a similar cohort of women receiving standard care. After reviewing the statistics from across South East Queensland, the most appropriate comparison cohort was women attending the Royal Brisbane and Women’s Hospital (RBWH) where senior managers and researchers agreed to collaborate on a joint project and funding submission. However, as the funding was being awarded, the RBWH also changed their model of care (2013) for Aboriginal and Torres Strait Islander women through the Ngarrama Indigenous Maternity Service and it is no longer standard care. The Ngarrama Service is a government-funded midwifery continuity of care service for women having an Aboriginal and/or Torres Strait Islander baby/ies and planning to birth at the RBWH (located fewer than six kilometres north of the MMH). Thus we have agreed to evaluate both new services, Birthing in Our Community and the Ngarrama Service, and will compare them to each other, and to women receiving standard care and to baseline data from both hospitals. (Note: not all women having Aboriginal and Torres Strait Islander babies at both MMH and RBWH access the Indigenous-specific models of care hence the concurrent comparison with standard care). Table 2 outlines the components of the different models of care available to women having Aboriginal and Torres Strait Islander babies at the MMH and RBWH. For the first time, researchers will test the effectiveness of caseload midwifery in an urban setting where 100% of the midwives’ caseload are women having Aboriginal and Torres Strait Islander babies receiving care across the maternity continuum (antenatal, birth, until 6 weeks postnatal).

**Table 2 Tab2:** Models of care available to Aboriginal and Torres Strait Islander families at study sites

Birthing in Our Community (Group 1)	Standard Care (Groups 2, 5)	Ngarrama Maternity Service (Group 4)

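### The comparison with 2009–2013 baseline data names no method that separates the new services' effect from calendar change, and its by-model form sets self-selected users against all earlier Indigenous women

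*Protocol article*

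**What the plan says.** All references are to the protocol article.

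- **Aims, Study setting and Study design** make the baseline comparison part of the evaluation. Routine outcomes since late 2013 are compared across groups "and to baseline data for both hospitals (2009–2013".
- **Quantitative** lists the comparators: the other new service, and "standard care (historical and concurrent control), and also non-Indigenous women and babies (historical and concurrent control) at MMH and RBWH". The methods named are bivariate tests for baseline differences, relative risks, regression and propensity score matching for confounders, generalized estimating equations for repeated measures, and mediation analysis. The example covariates are socio-economic and clinical. Analysis is by model of care.
- **Table 3** carries the label "Group 2: Standard care, MMH (Indigenous" from 2009 to 2019, and Group 5 likewise at RBWH. Groups 1 and 4 have no baseline years. The routine data row reads "Routine Data (2, 3, 5, 6" for baseline and "Routine Data (1–6" for the study period.
- **Study setting** notes that "not all women having Aboriginal and Torres Strait Islander babies at both MMH and RBWH access the Indigenous-specific models of care", which is its reason for having a concurrent standard-care group. It also says that RBWH changed its own model in 2013.
- **Quantitative** and the eligibility text for routine data remove women without antenatal care: "those with no antenatal care will be excluded from analysis". Attending five or more antenatal visits is one of the four primary outcomes.

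**The concern.** Three features of the written plan meet in the historical contrast.

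1. **Time.** Groups 1 and 4 exist only after late 2013, and the baseline exists only before. In a direct contrast of the two, model of care and era are the same variable. Adjustment for age, parity or socio-economic status does not remove a general change in smoking, attendance or preterm birth. Both hospitals changed their Indigenous service at about the same time, so neither keeps an Indigenous cohort that could show the trend without a new service.
2. **Make-up.** At baseline, Groups 2 and 5 are the only Indigenous groups shown at each hospital. Later they are the women who did not use the new service, and Groups 1 and 4 are those who did. A by-model historical contrast therefore sets a self-selected part against the whole. Measured covariates remove only some of that difference.
3. **No-care women.** A woman with no antenatal visits necessarily fails the five-visit outcome. If a service brings such women into care, they enter the later denominator while their earlier counterparts have been deleted, so a real gain can be partly hidden.

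Compared directly, the non-Indigenous groups measure the disparity. Their change over time is what bears on trend, and the article does not say it will be used that way.

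**Working it through.** **1. The plan's own figure.** Inputs from Table 4: preterm birth 16% to 9%, 350 per arm. With a two-sided 0.05 test and pooled variance under the null, the null standard error is √(2 × 0.125 × 0.875 / 350) = 0.0250, so the critical difference is 1.96 × 0.0250 = 0.0490. The standard error under the alternative is √[(0.16 × 0.84 + 0.09 × 0.91) / 350] = 0.0249. Power = Φ[(0.070 − 0.049) / 0.0249] = 0.801, as stated. This is the power of a plain two-group contrast with no allowance for time.

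**2. Drift alone (assumed; the article gives no trend).** The era midpoints are about mid-2011 and early 2017, 5.5 years apart. A drift of 0.25, 0.5 or 1.0 points per year gives 1.4, 2.75 or 5.5 points, against planned effects of 7 to 11 points in Table 4. The same test, with no programme effect and 350 per period, is significant with these probabilities (nominal 0.05):

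| Assumed fall, preterm from 16% | Probability | Assumed fall, smoking from 42% | Probability |
|---|---|---|---|
| 1 point | 0.065 | 2 points | 0.084 |
| 2 points | 0.115 | 4 points | 0.190 |
| 3 points | 0.203 | 6 points | 0.370 |
| 4 points | 0.332 | 8 points | 0.588 |

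**3. Make-up alone (assumed).** Suppose there is no effect, the overall preterm rate stays at 16%, half the women take up the service, and takers have an underlying risk r. The residual standard-care risk is (0.16 − 0.5r) / 0.5.

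| r | Residual risk | Spurious RR vs baseline (r / 0.16) | Spurious RR vs concurrent standard care |
|---|---|---|---|
| 14% | 18% | 0.88 | 0.78 |
| 13% | 19% | 0.81 | 0.68 |
| 12% | 20% | 0.75 | 0.60 |

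These are unadjusted; the planned adjustment would remove the measured part. The last column shows that concurrent contrasts share the self-selection problem.

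**4. No-care exclusion (assumed).** Read Table 4's 81% and 90% for five or more visits as rates among women with some care, and let z0 and z1 be the no-care proportions in the two eras. The difference among all women is 0.90(1 − z1) − 0.81(1 − z0). For (z0, z1) = (1%, 0.25%), (2%, 0.5%) and (4%, 1%) it is 9.6, 10.2 and 11.3 points, against 9.0 after exclusion. The article does not say which denominator Table 4 uses. The sum also holds both rates fixed, although women newly brought into care could pull the later rate down. It shows direction and rough scale only.

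**5. Power of a trend-controlled analysis.** Take 16% to 9% with 350 per period, and non-Indigenous women at 8% in both periods (the national figure in Background) with m per period (assumed; the article gives no number). The standard error is √[(0.16 × 0.84 + 0.09 × 0.91) / 350 + 2 × 0.08 × 0.92 / m], and power is Φ(0.07 / SE − 1.96).

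| m per period | SE | Power |
|---|---|---|
| 350 | 0.0322 | 0.58 |
| 1,000 | 0.0277 | 0.72 |
| 5,000 | 0.0254 | 0.79 |
| 20,000 | 0.0250 | 0.80 |

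These figures assume the full 7-point effect, before any dilution from partial uptake.

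**The case against.** The strongest reply is that this is a condensed article. The covariates are given as examples, confounders are not listed in full, and a calendar-year term may sit in a plan that is not shown. That is fair, and silence about year alone would not be a finding. But the article does fix the comparison with 2009–2013, analysis by model of care, and the no-care exclusion. With no baseline years for Groups 1 and 4, a year covariate in the direct contrast could only extrapolate the baseline trend. Identification needs a group that spans both eras and is untouched by the services.

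Several stronger readings are tempting, and the article does not support them.

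- A reader might infer that the whole evaluation is confounded with time. Concurrent contrasts with standard care and between the two services are planned, and calendar drift does not affect them.
- A reader might infer that make-up is not controlled at all. Regression and propensity score matching are planned and address measured differences.
- A reader might infer from the unbroken bars in Table 3 that Groups 2 and 5 will be pooled across eras. No text says so; the table separates baseline from study period.
- A reader might think the non-Indigenous cohorts solve both problems. They can address trend only. They say nothing about which Indigenous women remain in standard care.
- A reader might take the non-Indigenous data as already in hand. The text is prospective ("Data on all women attending either hospital during the study period will be extracted"), and that sentence names only the study period; baseline coverage comes from Table 3.

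It is also true that a hospital-level effect is a different estimand from the effect in women receiving the new model. It should therefore be added to the model-level contrasts and not replace them.

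**Conclusion.** The concern stands for the historical contrast. As written, that contrast mixes the services' effect with calendar change and with selection into the services, and the named adjustments reach only measured differences between women. The no-care exclusion pushes the visits outcome the other way, towards hiding a gain, so the net direction cannot be known from the article.

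The size cannot be known either. Drift, uptake, takers' risk and no-care proportions are all assumptions. One drift range should not be read as equally plausible for every outcome: at 1 point per year, preterm birth would fall from 16% to 10.5% with no programme. What the ranges do show is that drift well below the planned effects raises the false-positive rate well above 0.05. The point is worth acting on because Table 3 already plans the data needed.

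**What to change.** Keep the model-level contrasts, and add one analysis for the baseline comparison.

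- **Population.** All Indigenous births at the hospital regardless of model: Groups 1 and 2 together at MMH, and 4 and 5 together at RBWH, against Group 2 and Group 5 respectively in 2009–2013. This all-births denominator handles make-up.
- **Estimate.** The change between eras minus the change in non-Indigenous women at the same hospital (Group 3 or 6), with calendar-year terms. This handles trend. Check parallel trends over the baseline years.
- **Scale.** Fix it in advance, because trends parallel on one scale need not be parallel on the other. An assumed 10% relative fall takes 16% to 14.4% and 8% to 7.2%, which leaves 1.6 − 0.8 = 0.8 points on the difference scale with no effect.
- **No-care women.** Retain them here, at least for the visits outcome, since no model of care has to be assigned. Keep the exclusion for the model-level contrasts.
- **Wording.** State that Groups 2 and 5 are different populations before and after the services began.

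The cost is one added regression per outcome on routine data already planned, with the exclusion relaxed for this analysis. The downsides should be stated. Partial uptake dilutes the effect (at an assumed 50%, 7 points becomes 0.5 × 7 = 3.5). Parallel trends are an assumption. Precision depends on non-Indigenous numbers that the article does not give: before dilution, power for preterm birth is about 0.58 with 350 per period and 0.79 with 5,000.
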